### Cohort participants

The ASSESS-AKI Study will enroll a diverse group of adults (age 18 to 89 years) and children (age one month to 18 years) with and without AKI from participating Clinical Research Center networks.

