#### Exclusion criteria

Exclusion criteria were selected to balance the goal of maximizing representativeness of the cohort, clinical accuracy of AKI, and feasibility in achieving the project goals. These criteria are detailed in Table 1. The data sources used to ascertain information on these criteria include electronic and paper medical records, other electronic databases, and patient interviews.

**Table 1 T1:** Inclusion and exclusion criteria for the ASSESS-AKI Study.

Inclusion criteria	Exclusion Criteria
Adult participants aged 18 years to 89 years.	Inability to provide informed or surrogate consent.
Children aged greater than one month to less than 18 years old at cohort entry.	Died prior to the three-month study visit.
Documented "baseline" serum creatinine defined as the outpatient, non-emergency department test value nearest to the index hospitalization within 7 and 365 days prior to admission using an IDMS-traceable serum creatinine assay.	Incarcerated, institutionalized, or otherwise unable to participate in the study within a home, community, or clinical setting.
In the TRIBE-AKI consortium, pre-operative serum creatinine results from an IDMS-traceable assay obtained within seven days before cardiac surgery can be used to define "baseline" kidney function for the subset of participants who are undergoing non-urgent cardiac surgery.	Enrolled in an active interventional study at the three-month in-person study visit.
For pediatric participants in TRIBE-AKI, a pre-operative serum creatinine concentration measured in the local hospital clinical laboratory among patients scheduled for elective cardiac surgery.	Actively pregnant or breastfeeding. Prior chronic hemodialysis, peritoneal dialysis (lasting ≥three months), or estimated GFR <15 ml/min/1.73 m2 not receiving renal replacement therapy. History of solid organ and/or hematopoietic cell transplants.
	Acute glomerulonephritis diagnosed clinically or by biopsy.
	Clinically significant urinary tract obstruction, confirmed by imaging.
	Hospitalization involving acute nephrectomy.
	History of multiple myeloma.
	Hepatorenal syndrome.
	Metastatic cancer or systemic cancer receiving active treatment.
	New York Heart Association Class IV heart failure prior to index admission.
	Predicted survival of 12 months or less as determined by the participant's treating physician or Clinical Research.
	Center Principal Investigator.

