### Statistical approach and power

The primary outcomes for the study are time-to-event outcomes, such as time to death, a renal event or a clinical cardiovascular event. Some of these events will be known exactly on a continuum and could be right-censored. Exact dates for the occurrence of some of the events, however, may only be known to occur within a specific time interval t_k_, k = 1, 2, 3, 4, 5 (t_1 _= 0-3 months, t_2 _= 3-12 months, t_3 _= 12-24 months, t_4 _= 24-36 months, t_5 _= 36-48 months). The endpoints of these five time intervals correspond to the planned in-person study visits. Therefore, the statistical analyses in these situations will invoke continuous time-to-event models that account for right-censored and interval-censored data.

The hazard function for a continuous time-to-event outcome is of the form

$$\lambda_{\text{ijk}}(\text{t};{\text{x}}_{\text{ijk}})=\lambda_{0}(\text{t})\exp({\text{x}}_{\text{ijk}}\beta )$$

where

(a) λ_ijk_(t; x_ij_) is the hazard function at time t with covariate vector x_ijk _for the k^th ^member of the j^th ^matched set within the i^th ^site, j = 1, 2,...,n_i_, and k = 0 (non-AKI), 1 (AKI),

(b) λ_0_(t) is the baseline hazard function,

(c) β is an unknown parameter vector, and

(d) x_ijk _is a vector of regressors of interest.

The regressors that will appear in x_ijk _for the primary statistical analyses are as follows using as examples different variables: binary indicator variables at month 0 for non-AKI/AKI status, CKD status, gender, Hispanic ethnicity, cardiovascular disease status, diabetes status and sepsis status; ordinal variables at month 0 for racial group (0 = white/European, 1 = Black/African American, 3 = Asian/Pacific Islander, 4 = Native American, 5 = Other/Admixed), eGFR (0 = 15 to 29, 1 = 30 to 44, 2 = 45 to 59, 3 = 60 to 89, 4 = 90-150) and albumin-to-creatinine ratio (0 = <0.15, 1 = 0.15 to 0.5, 2 = >0.5 to 1.0, 3 = >1.0 to 3.0, and 4 = >3.0), age (0 = 1 to 17, 1 = 18 to 39, 2 = 40 to 49, 3 = 50 to 59, 4 = 60 to 69, 5 = 70 to 79, 6 = 80 to 89).

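### Racial group is specified as an ordinal score with arbitrary, gapped codes in the primary hazard model, and the lowest age code does not cover the youngest eligible children

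*Protocol article*

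**What the plan says.** The section Statistical approach and power gives a proportional hazards form with a covariate vector x_ijk and then lists what goes into it. Binary indicators come first: AKI, CKD, gender, Hispanic ethnicity, cardiovascular disease, diabetes and sepsis. A second group follows: "ordinal variables at month 0 for racial group (0 = white/European, 1 = Black/African American, 3 = Asian/Pacific Islander", then code 4 for Native American and code 5 for other or admixed. Baseline eGFR, albumin-to-creatinine ratio and age stand in that same group. The age codes begin "age (0 = 1 to 17, 1 = 18 to 39, 2 = 40 to 49". The list is introduced as the regressors "for the primary statistical analyses are as follows using as examples different variables".

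The section then replaces the simple model by a bivariate frailty model for the event and death. That model keeps x_ijk in both equations, so the coding carries over.

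On paediatric eligibility, Cohort participants admits "children (age one month to 18 years) with and without AKI", and Table 1 under Exclusion criteria has "Children aged greater than one month to less than 18 years old at cohort entry".

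Matching is described under Initial screening and enrollment of participants. It requires centre and CKD status. It attempts cardiovascular disease, diabetes, eGFR category, age category and ICU location. Race appears in neither set.

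**The concern.** Race is nominal. If the codes enter x_ijk as one number with one coefficient, the log hazard ratios against White for codes 1, 3, 4 and 5 must stand in the ratio 1 : 3 : 4 : 5. Neither the order nor the gap at 2 has a meaning, so the fit depends on labels.

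The study aims to isolate the independent effect of AKI. Since race is not matched on, this regression term is the only described means of controlling for it. A badly formed term can leave confounding by race in the AKI hazard ratio.

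The age point is smaller and separate. The adult bands imply that the unit is years, so a child aged 1 to 11 months is eligible but has no listed age code.

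**Working it through.** **1. The plan's own figure.** Inputs from the power statement: 1,200 participants (600 per group), 15% withdrawal, two-sided 0.05, relative risk 1.35 at an AKI event rate of 30% and 1.90 at 10%.

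- Evaluable per group: 600 × 0.85 = 510.
- Non-AKI rates: 0.30/1.35 = 0.222 and 0.10/1.90 = 0.0526.
- Two-proportion test: power = Φ{[|p1 − p2|√n − 1.96√(2p̄(1 − p̄))] / √(p1(1 − p1) + p2(1 − p2))}.
- Results: 80.8% and 81.4%.

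The stated power above 80% reproduces. The race and age codes do not enter this calculation.

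**2. What a single score imposes.** With a hazard ratio of b per unit, the hazard ratios against code 0 are b, b³, b⁴ and b⁵. For b = 1.5 (an illustration) these are 1.50, 3.38, 5.06 and 7.59. Consecutive codes 0 to 4 would instead give 1.50, 2.25, 3.38 and 5.06. Skipping a label therefore changes the model.

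**3. Effect on the AKI estimate.** The article gives no race distribution, so all of the following is assumed:

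- Shares for codes 0, 1, 3, 4, 5 are 70, 15, 8, 2 and 5%.
- Only the code 1 group differs from the rest.
- The AKI log-odds are −0.1 in the other groups.
- The hazard is 0.06 per year over 4 years, with a true AKI hazard ratio of 1.

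Scenario A sets both the hazard ratio and the AKI odds ratio of the code 1 group at 1.5. Scenario B sets both at 2.0.

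With no race term:

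- P(AKI) in the other groups is 1/(1 + e^0.1) = 0.475. In the code 1 group it is 0.576 (A) or 0.644 (B).
- A: the code 1 share among AKI is 0.0864/0.490 = 0.176, and among non-AKI 0.0636/0.510 = 0.125. AKI hazard ratio ≈ (1 + 0.5 × 0.176)/(1 + 0.5 × 0.125) = 1.024.
- B: the shares are 0.193 and 0.107. AKI hazard ratio ≈ 1.193/1.107 = 1.078.

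The score barely tracks membership of the code 1 group:

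- Mean score = 0.15×1 + 0.08×3 + 0.02×4 + 0.05×5 = 0.72.
- Variance = 2.44 − 0.72² = 1.92.
- Covariance with the code 1 indicator = 0.15 × (1 − 0.72) = 0.042; variance of the indicator = 0.15 × 0.85 = 0.1275.
- r² = 0.042²/(1.92 × 0.1275) = 0.007.

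A simulation of 1,000,000 subjects with a constant-hazard regression gave these AKI hazard ratios:

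| Race term | A | B |
|---|---|---|
| None | 1.024 | 1.078 |
| Score 0/1/3/4/5 | 1.024 | 1.078 |
| Indicators | 1.001 | 1.006 |

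The simulation error on the log scale is about 2/√213,000 = 0.004, taking an event fraction of 1 − e^(−0.24) = 0.213. The last row is therefore compatible with 1.

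Against the smallest effect the study is sized for, a relative risk of 1.35, the bias on the log scale is 0.024/0.300 = 8% (A) or 0.075/0.300 = 25% (B).

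**4. Age.** Eligibility starts at one month and the lowest code starts at 1. The planned children number 50 + 50 = 100, and 100/1,200 = 8.3% is the ceiling on those affected. The article does not say how many are under one year. The Cardiovascular outcomes section restricts those outcomes to adults, so they are untouched.

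**The case against.** The article never states that there is one coefficient per unit. It gives category codes and an unspecified parameter vector, and its introduction calls the variables examples. The codes could be class labels, the missing 2 could be a misprint, and an analysis plan that is not shown could settle the matter. This stands in part: the single-score reading is the natural one, because these variables are set apart from the binary indicators, but it is not proved. If class levels were meant, the word ordinal is still wrong for race.

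Four stronger readings are tempting, and the document does not support them:

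- **Race is not adjusted for.** Race is in the model, and Hispanic ethnicity has its own indicator. The fault is the form of the race term.
- **Infants drop out of the analysis.** Nothing says so. It would need the unit to be years, a child under one year to be left uncoded rather than coded 0, and a complete-case fit. Code 0 is evidently the paediatric category, since the next begins at 18.
- **The model would report hazard ratios of 3.4 to 7.6.** These follow from fixing one contrast at 1.5. A fitted slope is estimated from all groups together, so the figures show the constraint and predict nothing.
- **Banding age and eGFR is an error.** The adult bands are also the categories on which matching is attempted, and adjusting on them is conventional. Continuous terms are a preference.

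It is also fair that a bias of 1.02 to 1.08 is modest beside target effects of 1.35 to 1.90.

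**Conclusion.** The point holds in limited form. As written, the primary model adjusts a nominal confounder by an arbitrary score, and the final bivariate model inherits that coding. If the score enters linearly, it can leave residual confounding by race that matching does not address. In the assumed scenarios this moved a null AKI hazard ratio to 1.02 or 1.08, against 1.00 or 1.01 with indicators. Those sizes rest on the assumed shares, on a single differing group and on the linear reading. Another race pattern would give other values, and a pattern that happened to follow the code order would give less bias.

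The age band contradicts the eligibility text. It is a drafting mismatch limited to the paediatric part, at most 8.3% of participants. Neither matter touches the sample size or the power statement.

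**What to change.** - Describe racial group as categorical and enter it as indicator variables with White as reference, pooling sparse groups. Five groups need up to 4 degrees of freedom instead of 1.
- Start the lowest age category at one month and print the unit, so that the codes agree with Cohort participants and Table 1.
- Optionally, model age, eGFR and albumin-to-creatinine ratio continuously. The correction does not depend on this.

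The cost is a change of analysis wording and up to three further degrees of freedom per equation. No new data are needed and the sample size stays as it is. The change should be recorded before the primary model is fitted.

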**Figure 2 F2:**
[figure not shown]
**Summary of identification and enrollment approach for AKI and Non-AKI participants**. The figure applies to adult participants only. Any eligible pediatric subject undergoing cardiopulmonary bypass-requiring cardiac surgery is approached for participation during the inpatient phase.

Given the matched parallel cohort design, we will identify and enroll a sample of hospitalized adult patients who did not appear to suffer an AKI episode and who are matched in a minimum 1:1 AKI:non-AKI ratio, with each non-AKI subject individually matched to their corresponding AKI subject on the following set of key confounding characteristics: Clinical Research Center and presence of baseline chronic kidney disease using an CKD-EPI[19] equation-estimated GFR threshold of <60 ml/min/1.73 m^2^. In addition, we will further attempt to match on the presence or absence of clinical cardiovascular disease, presence or absence of diabetes mellitus, category of baseline eGFR (15-29, 30-44, 45-59, 60-89, 90-150 ml/min/1.73 m^2^), adult age category (18-39, 40-49, 50-59, 60-69, 70-79, 80-89 years), and hospital location where AKI episode occurred (ICU versus non-ICU).

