#### Incident CKD

Among participants without pre-existing CKD at the index hospitalization, we will examine time to development of incident CKD with significant loss of renal function defined as experiencing both a minimum 25% reduction in level of eGFR compared with baseline and achieving CKD Stage 3 or worse[37] during follow-up.

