#### Progression of CKD

Among participants with pre-existing CKD at the index hospitalization (defined as an eGFR <60 ml/min/1.73 m^2^), we will examine time to progression of CKD, defined as experiencing at least a 50% reduction in level of eGFR compared with baseline or progressing to CKD Stage 5 [37].

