The hazard model described above, however, is not the final form of the hazard model that will be applied in this study. Instead, the hazard model needs to account for (1) the dependency between an AKI subject and a non-AKI subject within a matched pair and (2) informative censoring. The occurrence of some of the renal and cardiovascular events may not be independent of the censoring event of death. For example, individuals who are censored because of death may have been at higher risk for renal and cardiovascular events. Therefore, a bivariate hazard function for the simultaneous modeling of the renal (or cardiovascular) event and death is invoked [54,55]. Let (T_ijk_, D_ijk_) denote the continuous time of a renal or cardiovascular event and the time of death, respectively, for the k^th ^member of the j^th ^pair within the i^th ^site, j = 1, 2,...,n_i_, and k = 0 (non-AKI), 1 (AKI). The bivariate hazard model is

$$\lambda_{\text{T,ijk}}(\text{t};{\text{x}}_{\text{ijk}})=\lambda_{\text{T0}}(\text{t})\exp({\text{x}}_{\text{ijk}}\beta_{\text{Ti}}+{\text{e}}_{\text{Tij}})\;\text{and }\lambda_{\text{D,ijk}}(\text{d};{\text{x}}_{\text{ijk}})=\lambda_{\text{D0}}(\text{d})\exp({\text{x}}_{\text{ijk}}\beta_{\text{Di}}+{\text{e}}_{\text{Dij}})$$

where the [e_Tij _e_Dij_]'s are independent and identically distributed according to a bivariate normal distribution with null mean vector and positive-definite variance matrix. The covariance between e_Tij _and e_Dij _represents the magnitude of the relationship between the occurrence of the renal (or cardiovascular) event and the censoring event of death. An estimated value of the covariance near zero indicates non-informative censoring, whereas an estimated value of the covariance distant from zero indicates informative censoring.

The sample size for the study is (1) 550 adult AKI subjects and 550 matched adult non-AKI subjects and (2) 50 pediatric AKI subjects and 50 pediatric non-AKI subjects, at the 3-month visit. For a two-sided, 0.05 significance level test of the relative risk equaling 1.0, the sample size of 1,200 yields greater than 80% statistical power, while allowing for a 15% withdrawal rate, for detecting a relative risk between 1.35 (when the event rate for AKI subjects is 30%) and 1.90 (when the event rate for AKI subjects is 10%).

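### Baseline eGFR enters the primary models only in the five matching bands, so avoidable residual confounding can remain in the renal event analyses

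*Protocol article*

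**What the plan says.** All references are to the protocol article.

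- **Baseline kidney function** requires a pre-admission creatinine for every participant and converts it to eGFR. The exact value is therefore in hand.
- **Statistical approach and power** lists eGFR among the ordinal regressors for the primary analyses, coded "eGFR (0 = 15 to 29, 1 = 30 to 44, 2 = 45 to 59", with codes 3 and 4 for 60 to 89 and 90 to 150. The other kidney regressors are a CKD indicator and banded albumin-to-creatinine ratio. The bivariate model that follows adds pair-level random effects but no finer eGFR term.
- **Initial screening and enrollment of participants** makes CKD status at eGFR 60 a firm matching factor. Matching on "category of baseline eGFR (15-29, 30-44, 45-59, 60-89, 90-150" is only attempted.
- **Incident CKD** requires "a minimum 25% reduction in level of eGFR compared with baseline and achieving CKD Stage 3" or worse. **Progression of CKD** requires "at least a 50% reduction in level of eGFR compared with baseline or progressing to CKD Stage 5".
- The **Discussion** says that CKD severity strongly predicts both AKI and CKD progression, and faults earlier studies for not controlling for it.

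**The concern.** Matching and regression use the same cut-points, so neither takes account of eGFR differences inside a band. The renal event rules make some of those differences matter, because the distance to the stage threshold depends on the exact baseline value.

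If AKI participants tend to have lower eGFR than non-AKI participants in the same band, they start closer to the threshold. They would then reach the outcome more often even if AKI had no effect. The excess would be read as an AKI effect, and the independent effect of AKI on kidney outcomes is a central question of the study.

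Inside each renal analysis the CKD indicator does not help, because the incident analysis is restricted to people without CKD and the progression analysis to people with it. In the incident analysis only codes 3 and 4 occur, so eGFR adjustment reduces to one split at 90.

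**Working it through.** **1. The plan's own figure.** The power statement is "For a two-sided, 0.05 significance level test of the relative risk equaling 1.0", where "the sample size of 1,200 yields greater than 80% statistical power", "while allowing for a 15% withdrawal rate". The groups are 600 each, and 600 × 0.85 = 510. The effects run from "a relative risk between 1.35 (when the event rate for AKI subjects is 30"%) to 1.90 (AKI rate 10%).
- RR 1.35: rates 30% and 30/1.35 = 22.2%; two-proportion power at 510 per group is 80.8%.
- RR 1.90: rates 10% and 10/1.90 = 5.3%; power is 81.4%.

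The statement reproduces. It does not depend on how eGFR is coded. It serves here as a yardstick: the smallest effect the study is sized to detect is a relative risk of 1.35.

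**2. Fall needed at baseline eGFR b.** Stage 3 is taken as eGFR below 60 and Stage 5 as below 15.
- Progression: 1 − max(0.5, 15/b)
- Incident CKD: 1 − min(0.75, 60/b)

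| Outcome | Band | Fall needed |
|---|---|---|
| Progression | 15–29 | 6% at 16, 25% at 20, 40% at 25, 48% at 29 |
| Progression | 30–44 and 45–59 | 50% throughout |
| Incident CKD | 60–89 | 25% from 60 to 80, then rising to 33% at 89 |
| Incident CKD | 90–150 | 33% at 90, 40% at 100, 50% at 120, 60% at 150 |

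The percentage fall therefore varies within 15–29, within 60–89 above 80, and within 90–150. It does not vary within 30–59.

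**3. Is a within-band difference plausible?** The Discussion links CKD severity to AKI risk. The AKI definition also accepts an absolute creatinine rise of 0.3 mg/dL. That is a 30% rise at creatinine 1.0 (0.3/1.0), 15% at 2.0 and 10% at 3.0, so a higher baseline creatinine makes the criterion easier to meet in relative terms. Both point to lower eGFR among AKI participants within a band. Neither measures the difference.

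**4. Size when AKI has no effect.** The following assumptions are not in the document:
- baseline eGFR about normal, mean 85, SD 25;
- AKI odds multiplied by 1.1 to 1.6 per 10 ml/min lower eGFR;
- log-eGFR slope per year with mean −0.03 and SD 0.06, and visit noise SD 0.10; alternatively mean −0.02, SD 0.05 and noise SD 0.05;
- groups exactly balanced on the five bands.

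Events were assessed at 3, 12, 24, 36 and 48 months. The spurious AKI relative risk left after band-only control is below; each range spans the two decline scenarios.

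| AKI odds ratio per 10 ml/min | AKI minus non-AKI eGFR in 15–29 (ml/min) | Progression | Incident CKD |
|---|---|---|---|
| 1.1 | −0.16 | 1.02–1.05 | 1.02 |
| 1.2 | −0.30 | 1.05–1.10 | 1.04 |
| 1.4 | −0.55 | 1.09–1.19 | 1.06–1.07 |
| 1.6 | −0.75 | 1.13–1.28 | 1.08–1.09 |

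Within single bands the range is 1.05–1.33 for 15–29 and 1.08–1.51 for 90–150. It is 1.00 in both bands between 30 and 59.

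A second set of assumptions used eGFR about N(42, 13) in the CKD group, and a follow-up/baseline ratio that is lognormal with mean log −0.1 and SD 0.25–0.35. For progression it gave 1.01–1.13 at odds ratios 1.1–1.4 and 1.08–1.19 at 1.6. In simulations of this kind, a spline in exact eGFR brought the hazard ratio back to 0.99–1.04 for progression and 0.99–1.01 for incident CKD.

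**5. Power with no imbalance, bands against spline.** Incident CKD: 0.588 against 0.583, and 0.805 against 0.805. Progression: 0.175 against 0.193, and 0.283 against 0.308. The change is at most about 3 percentage points, so the gain is in bias and not in power.

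**The case against.** **Within-band imbalance is not documented.** This stands. The article gives no eGFR distribution by AKI status within bands. Attempted matching on age, diabetes, cardiovascular disease and ICU location may narrow the difference. Exclusion of participants who die before, or have ESRD at, the three-month visit removes some with low eGFR. A reader might infer that the coding certainly biases the AKI effect in both renal outcomes. The document supports only that it can, and that the likely direction is away from the null.

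**Larger figures need a stronger imbalance.** A 1.5 ml/min within-band difference was simulated to give a progression hazard ratio of 1.14–1.37. Under the second set of assumptions, that difference in the 15–29 band requires an AKI odds ratio of about 2.5–3 per 10 ml/min. Nothing in the document supports a value that high.

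**The reach is narrow.** This stands. For progression only the 15–29 band is affected, about 18% of the CKD group under N(42, 13). The mechanism does not concern death or cardiovascular events. The calculations also omit the albumin-to-creatinine ratio and the other regressors, which could absorb part of the difference.

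**The codes may be category labels.** A reader might infer that the 0–4 score forces equal log-hazard steps. The article does not say so: it lists racial group under the same ordinal heading, and that variable is plainly nominal. The point does not need this claim, since class variables would ignore within-band differences just as a linear score does.

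**The regressor list is worded partly as examples.** This gives some room, and functional form is often settled in an analysis plan. But the eGFR cut-points are explicit and given for the primary analyses, so this is stated coding and not an omission. The Discussion's general caveat about residual confounding does not answer the point either, because this part is avoidable with data already required.

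**Conclusion.** The point holds as avoidable residual confounding in the renal event analyses. The exact value, the five-band coding, the shared cut-points and the within-band differences in needed fall all follow from the document, given the usual stage limits of 60 and 15.

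The size depends on assumptions. For AKI odds ratios of 1.1 to 1.6 per 10 ml/min lower eGFR, the spurious relative risk is roughly 1.02–1.1 for incident CKD and 1.01–1.28 for progression. That is modest for incident CKD against the smallest detectable relative risk of 1.35. For progression the upper end comes close to it. The change is worth making, but it does not undermine the design or the sample size.

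**What to change.** In the regressor list under Statistical approach and power, replace the eGFR codes with baseline eGFR as a continuous variable in a flexible form, for example a restricted cubic spline. Do this in the primary hazard models, at least for incident CKD and progression of CKD. Keep the five bands for matching and for descriptive tables.

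The cost is a wording change and two or three extra parameters, with no new data, visits or participants. The one drawback is the use of those degrees of freedom in the CKD subgroup, where events may be few. Exact knot placement is a modelling preference. Treating age in the same way is optional; no calculation here supports it.

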While ASSESS-AKI has numerous strengths, it also has several limitations. The cohort will be enriched with patients suffering AKI in common at-risk settings such as surrounding cardiac surgery or within the ICU as well as in more general hospitalized settings, but we will have limited power to examine whether the clinical setting modifies the association between AKI and clinical outcomes. The inclusion of children expands the age range being evaluated but is only applicable to those requiring cardiopulmonary bypass. The relatively small number of children targeted for enrollment means we will be able to detect only large effect sizes. The multi-center cohort includes various U.S. and Canadian sites and health care delivery systems, but the results may not be generalizable to all practice settings and populations. Despite various design and analytic approaches as well as standardized data collection and quality control efforts, as an observational study, we cannot rule out the impact of residual confounding and bias. However, since a randomized comparison is not possible, our prospective cohort design and systematic follow-up will provide a rigorous assessment among eligible participants. There are ongoing plans to address some of these limitations by augmenting ASSESS-AKI with possible ancillary studies (e.g., recruitment of a larger number of pediatric patients).

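### The final hazard model links event and death only through a frailty shared by the matched pair, so a near-zero covariance does not show that censoring by death is non-informative

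*Protocol article*

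**What the plan says.** The section Statistical approach and power first writes a proportional hazards model with a single coefficient vector β. It then replaces that model, because the final one has to deal with two things: "the dependency between an AKI subject and a non-AKI subject within a matched pair and (2) informative censoring". The reason for the second is given at the level of the person: "individuals who are censored because of death may have been at higher risk for renal and cardiovascular events".

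Event and death times are indexed T_ijk and D_ijk, for member k of pair j at site i. The final linear predictors are x_ijk β_Ti + e_Tij for the event and x_ijk β_Di + e_Dij for death. The pairs of random effects are "independent and identically distributed according to a bivariate normal distribution with null mean vector and positive-definite variance matrix". The article states that their covariance "represents the magnitude of the relationship between the occurrence of the renal (or cardiovascular) event and the censoring event of death" and then gives the reading rule: "An estimated value of the covariance near zero indicates non-informative censoring, whereas an estimated value of the covariance distant from zero indicates informative censoring".

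The power statement at the end of the section concerns one relative risk: "For a two-sided, 0.05 significance level test of the relative risk equaling 1.0".

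**The concern.** The only random effects have no k. One term is asked to do two jobs, pair dependence and informative censoring, and it sits at the level that suits only the first. Given covariates and the pair effect, a person's own event and death are treated as independent. Conditional independence given a frailty is normal in such models. The problem is that the frailty here belongs to two different people.

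Two things are at stake. The reading rule could lead the investigators to report that death did not censor informatively when it did. The AKI hazard ratio for renal and cardiovascular events could also be somewhat off.

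A smaller point lies in the same equations. The coefficients carry the site index i, which conflicts with the common β a few lines earlier and with the single relative risk in the power statement.

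**Working it through.** **1. The plan's own figure.** The stated power is above 80% for 600 per group with 15% withdrawal, so 600 × 0.85 = 510 per group. The check is a two-sided 0.05 test of two proportions with pooled variance.
- AKI rate 30%, relative risk 1.35: the non-AKI rate is 0.30/1.35 = 22.2% and power is 80.8%.
- AKI rate 10%, relative risk 1.90: the non-AKI rate is 0.10/1.90 = 5.26% and power is 81.4%.

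The figure reproduces. It assumes one common effect and does not bear on the frailty.

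**2. What the indices imply.** Suppose the true log-hazard effects are a pair part plus a person part, with event-death covariances c_pair and c_person.
- A person's own event and own death: covariance c_pair + c_person.
- A person's event and the partner's death: covariance c_pair.

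The article's model has one parameter, Cov(e_Tij, e_Dij), for both. It makes a person's death as informative about the partner's event risk as about the person's own. If c_pair is small and c_person is large, no single value fits both, and the estimate is pulled below c_pair + c_person.

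**3. How much may be shared.** The enrolment section matches on Clinical Research Center and CKD and, where possible, on cardiovascular disease, diabetes, eGFR category, age category and ICU location. Five of these seven (CKD, cardiovascular disease, diabetes, eGFR, age) are among the listed regressors. Center and ICU location are not, and the regressors are given as examples. The shared fraction is therefore unknown, so it was varied.

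**4. Simulated size.** Assumptions that are not in the documents: 4 years of follow-up; event risk about 22% (non-AKI) and 29% (AKI); death risk about 20% and 25%; AKI hazard ratio 1.5 for the event and 1.3 for death; normal frailties with SD 1; true within-person covariance 0.80.

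| Frailty variance shared by the pair | Pair-level model (as written) | Person-level model |
|---|---|---|
| 0% | 0.20–0.21 (0.14 with piecewise baseline) | 0.77–0.84 |
| 25% | 0.33–0.35 | 0.73–0.88 |
| 50% | 0.50 | 0.82 |
| 100% | 0.74–0.83 | 0.77–0.80 |

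With 600 pairs, nothing shared and 200 runs, the 5% likelihood-ratio test of zero covariance rejected as follows.

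| True covariance | Pair-level: rejects (median estimate) | Person-level: rejects (median estimate) |
|---|---|---|
| 0.8 | 70.5% (0.215) | 97% (0.836) |
| 0.4 | 23% (0.12) | 60.5% (0.42) |
| 0 | 1% (0.02) | 5.5% (0.01) |

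At a true covariance of 0.4, the pair-level test thus misses real within-person dependence in 77% of runs. When the true covariance was zero and 25% or 50% of the frailty was shared, it rejected in 4% and 8%.

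**5. Effect on the AKI hazard ratio.** With nothing shared, the pair-level mean log hazard ratio was 0.362 against a true 0.405, that is exp(0.362) = 1.44 against 1.50. It was the same 0.362 at covariance 0, 0.4 and 0.8, so in this setting the shortfall comes from omitted person-level heterogeneity.

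To isolate death-related bias, the true event hazard ratio was set to 1.0, where omitted heterogeneity alone causes no attenuation. The death hazard ratio was set to 2.0 (24 runs of 3,000 pairs, SE of the log hazard ratio about 0.015).

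| True covariance | Pair-level | Person-level |
|---|---|---|
| 0 | 0.998 | 0.991 |
| 0.8 | 0.956 | 0.991 |
| 1.0 | 0.940 | 0.983 |

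Here log(0.956) = −0.045, about 3 SE below zero. Some death-related bias therefore remains when AKI strongly raises mortality, and it runs towards hiding harm from AKI.

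**6. Site index.** The listed regressors number 7 binary + 4 ordinal = 11. Taken literally, three networks need 11 × 3 = 33 event coefficients. Expected events are 510 × (0.10 + 0.0526) = 78 at the lower rate and 510 × (0.30 + 0.222) = 266 at the higher rate.

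**The case against.** A reader might infer that the model cannot measure or correct informative censoring at all and that its covariance test is void. The documents and the figures above do not support that. The model captures whatever dependence the pair shares, nearly in full when all frailty is shared, and it picks up a diluted part of purely person-level dependence. Under zero covariance it rarely rejected. The half of the reading rule about values far from zero broadly stands.

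A reader might also infer that the main AKI estimate is seriously biased by death. The shortfalls seen are about 4 to 6%, part of that is omitted heterogeneity, and all of it rests on assumed frailty sizes. Time to death is itself listed as a primary outcome and is not censored by death.

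The missing k could be a printing slip. That does not rescue the text: with e_Tijk and e_Dijk alone, the pair dependence would have no term. The enrolment and sample-size text also describes matching only for adults, so the pair index is undefined for the children, whom the age regressor includes.

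The site index may equally be a slip. Subscripts in this section are loose (x_ij appears where x_ijk is meant, and k denotes both time interval and pair member), and no sentence announces site-specific effects. The Discussion's remark that "we will have limited power to examine whether the clinical setting modifies the association between AKI and clinical outcomes" concerns clinical setting as an effect modifier, so it is not evidence for site-specific coefficients. The count of 33 coefficients on 78 events is a worst case.

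Finally, this is a condensed article that cites sources for the model, and any analysis plan is not shown. That excuses missing detail. It does not excuse an equation and a reading rule that are printed and do not fit together.

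**Conclusion.** The point holds in a limited form. The frailty sits on the pair while the stated problem sits on the person, so the covariance is not the individual event-death relationship that the article says it is. It understates the within-person part: about 0.2 for a true 0.8 when the pair shares nothing, close to the truth when the pair shares everything. A near-zero estimate is therefore no evidence of non-informative censoring, whereas a clearly non-zero one still signals dependence.

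Attenuation of the AKI hazard ratio is secondary and modest in the scenarios tried. These sizes depend on frailty variances, a shared fraction and a mortality effect that the documents do not give. The site-indexed coefficients are an inconsistency of notation to correct, and they do not show that no common AKI effect will be estimated.

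**What to change.** - Add person-level correlated terms, e_Tijk and e_Dijk, or one shared person frailty with a loading in the death hazard, so that the event-death link belongs to the individual.
- Carry pair dependence separately, by a pair effect or by a variance clustered on the matched set. Say how unmatched children enter.
- Reword the covariance sentence so that a value near zero is not taken as proof of non-informative censoring, and present the covariance as a sensitivity measure.
- Write common coefficients β_T and β_D for the main AKI effect, in line with the first model and the power statement. Keep any AKI-by-center interaction secondary.

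The cost is plan wording and heavier computation; no new data are needed. Variance components may be imprecise when events are few (about 78 at the lower planning rate). A model with both person and pair effects was not fitted here, so it should be tried on simulated data of the study's size before it is fixed. The clustered variance is the simpler option if it proves unstable.
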